***12.2.9. Safety Analyses***

Safety analysis will include all randomized patients who take at least one dose of study drug.

The variables included in the safety analysis will include, but not necessarily be restricted to, those listed in Table LYDZ(b).4.

Safety will be assessed by summarizing and analyzing adverse events, vital signs, weight, ECGs, and concomitant medications use.

**Table LYDZ(b).4. Description of Safety Variables**

Analysis Variable Description

1.Change from baseline to last observation:

a. Vital signs and weight b. ECGs

2. Indicator variable for:

a. Serious adverse events

b. Discontinuations due to adverse events c. Treatment-emergent adverse events

1. Difference between baseline and last observation on study drug (LOCF change scores). Only patients having a baseline and at least one post-baseline measure that have taken at least 1 dose of study drug will be included in the analysis. a. N/A

b. ECG interval times and heart rate QTc intervals will be analyzed using the Fredericia’s correction factor and a data-based correction factor.

2.

a-b. N/A

c. A treatment-emergent adverse event is an adverse event that first occurred or worsened post- baseline.

3. Concomitant medications 3. N/A

4. Dosing 4. Mean, final and modal dose

5. Exposure 5. Summarized by visit

Variables 1.a-1.b will be compared across treatment groups using a fixed effects ANCOVA model incorporating treatment and investigator effects and baseline as a covariate using the raw observation as the dependent variable. Variables 2.a-2.c and 3 will be analyzed by comparing frequencies for each treatment group using Fisher’s Exact test. Baseline for determining treatment emergence will be defined as Visit 1 through Visit 2. The treatment period for determining treatment emergence will be defined as Visit 3 through Visit 6.

Mean, modal, and final doses will be tabulated for the atomoxetine arm. Exposure to study drug will be tabulated for both treatment groups.

Categorical analyses of vital signs and ECGs will be performed using the clinically significant thresholds defined in the atomoxetine integrated summary of safety.

Time to discontinuation will be compared across treatment groups in a similar manner to that used for time to response and time to remission.

These safety measures will be summarized separately during Study Period III.

***12.2.10. Subgroup Analyses***

The subgroup analyses will include analyses between each subgroup of patients as well as statistical models that test for subgroup effects and treatment by subgroup interaction.

Subgroups of patients for efficacy analyses will include investigational site, prior- stimulant-use strata, ADHD subtype, gender, and age.

For investigational site subgroup analyses (pooled as described in Section 12.2.1.1), changes in CAARS-Inv-SV total ADHD symptom score will be assessed using an ANCOVA model, including terms for baseline, treatment, subgroup, and the treatment- by-subgroup interaction. If the interaction is statistically significant at the 0.10 level, then the potential causes of the interaction will be investigated.

The incidence of treatment-emergent adverse events (TEAE) will be summarized by the following subgroups; investigational site, prior-stimulant-use strata, ADHD subtype, gender, and age.

***12.2.11. Interim Analyses***

No interim analyses are planned for this study. If an unplanned interim analysis is deemed necessary, the appropriate Lilly regulatory scientist will be consulted to determine whether it is necessary to amend the protocol.

Only the data monitoring committee (DMC) is authorized to review completely unblinded interim efficacy and safety analyses. Study sites will receive information about interim results ONLY if they need to know for the safety of their patients.

At the end of Study Period III, all data will be brought in house and locked. This will not be considered an interim analysis since this is considered the final lock of the study.

Study Period II data will be analyzed separately from Study Period III, the open label portion of this trial. It may be possible for the CS to continue after the final lock has occurred for this trial. This will not impact the final lock on the CS as this is completely separate from the trial and will not impact the planned analyses.

**13. Informed Consent, Ethical Review, and Regulatory**

**Considerations**

**13.1. Informed Consent**

For this study, privacy statement/opt-in consents and informed consents are obtained and electronically signed online via the study website. Prior to the first level of screening (completion of ASRS scale to determine likelihood of meeting ADHD criteria), a waiver with a privacy statement/opt-in consent is obtained. If the subject has a positive score on the ASRS at the first level of screening, they must opt-in via the study website prior to completing questions regarding inclusion/exclusion criteria (the second level of screening for the study). This opt-in statement will provide a brief overview of the RCT and CS,

though the subject will not electronically sign the consent for the RCT or CS until after completing the inclusion/exclusion criteria survey. After completion of the inclusion/exclusion criteria questions, the subject will be informed of eligibility for the RCT. If the subject is eligible for and chooses to participate in the RCT, an informed consent will be obtained at the investigator site by qualified site personnel. Similarly, if the subject opts-in for the CS, an online self-administered informed consent will be

obtained prior to entry into the CS.

Both the RCT and CS in this study utilize the rating of an “observer” identified by the patient. A self-administered informed consent will be obtained online via the study website from the person identified as the observer to complete the driving behavior rating scale. Additionally, the observer will do all driving behavior ratings through the study website.

For the RCT, the investigator is responsible for ensuring that the patient understands the risks and benefits of participating in the study, including answering any questions the patient may have throughout the study and sharing in a timely manner any new information that may be relevant to the patient's willingness to continue his or her participation in the trial.

The informed consent document will be used to explain the risks and benefits of study participation to the patient in simple terms before the patient is entered into the study, and to document that the patient is satisfied with his or her understanding of the risks and benefits of participating in the study and desires to participate in the study.

The investigator is responsible for ensuring that informed consent is given by each patient. This includes obtaining the appropriate signatures on the ICD prior to the performance of any protocol procedures and prior to the administration of study drug.

**13.2. Ethical Review**

Lilly must agree with all ICDs before they are submitted to the ERB and are used at investigative sites(s). All informed consent documents must be compliant with the

International Conference on Harmonization (ICH) guideline on good clinical practice (GCP). Informed consent obtained under special circumstances may occur only if allowed by local laws and regulations and performed in accordance with a written process approved by Lilly.

Documentation of ERB approval of the protocol and the ICD must be provided to Lilly *before* the study may begin at the investigative site(s). The ERB(s) will review the protocol as required.

Any member of the ERB who is directly affiliated with this study as an investigator or as site personnel must abstain from the ERB’s vote on the approval of the protocol.

The study site’s ERB should be provided with the following:

• the current Investigator’s Brochure or package labeling and updates during the course of the study

• Informed Consent Document

• relevant curricula vitae.

**13.3. Regulatory Considerations**

This study will be conducted in accordance with the ethical principles that have their origin in the Declaration of Helsinki and that are consistent with good clinical practices and the applicable laws and regulations. The investigator, head of the medical institution, or designee will promptly submit the protocol to applicable ERB(s).

Atomoxetine is being studied in the United States (US) under a US Investigational New

Drug (IND) application. The US IND number is 19,228.

All or some of the obligations of the sponsor may be assigned to a contract research organization (CRO).

An identification code assigned by the electronic data capture system to each patient will be used in lieu of the patient's name to protect the patient's identity when reporting adverse events and/or other trial-related data.

***13.3.1. Investigator Information***

Board-certified or eligible physicians (MD or DO) with clinical research experience who are qualified to evaluate and treat adult ADHD patients will participate as investigators in this clinical study. Clinical psychologists with similar research and clinical skills can

also serve as a principal investigator provided he/she works with a sub-investigator who

is a qualified physician (MD or DO).

***13.3.2. Protocol Signatures***

After reading the protocol, each principal investigator will sign the protocol signature page and send a copy of the signed page to a Lilly representative.

***13.3.3. Final Report Signature***

The sponsor’s responsible medical officer will sign the final clinical study report for this study, confirming that, to the best of his or her knowledge, the report accurately describes the conduct and results of the study.

**Protocol Attachment LYDZ(b).1.**

**Study Schedule**

**Study Schedule, Protocol B4Z-US-LYDZ(b)**

| **Study Period** | **I** | | **II** | | | | **III** | | |
| --- | --- | --- | --- | --- | --- | --- | --- | --- | --- |
| **Visit** | **1** | **2** | **3** | **4** | **5** | **6**  **SUM IIa** | **7** | **8** | **9**  **SUM IIIa** |
| **Weeks Until Next Visit:** | **1** | **2** | **3** | **3** | **4** | **2** | **5** | **5** | **N/A** |
| **Interval Between Visits and**  **Target ( )** | **5-28 (7)** | **10-18 (14)** | **17-25 (21)** | **17-25 (21)** | **25-31 (28)** | **10-18 (14)** | **28-38 (35)** | **28-38 (35)** | **-** |
| Informed consentb | X |  |  |  |  |  |  |  |  |
| Patient number assigned | X |  |  |  |  |  |  |  |  |
| Inclusion/exclusion criteria  (including PHQ-9) | X |  |  |  |  |  |  |  |  |
| Presenting/preexisting conditionsc | X |  |  |  |  |  |  |  |  |
| Medical/psychiatric history | X |  |  |  |  |  |  |  |  |
| Physical Exam | X |  |  |  |  |  |  |  |  |
| Height | X |  |  |  |  |  |  |  |  |
| Weight | X | X | X | X | X | X | X | X | X |
| Vital signs | X | X | X | X | X | X | X | X | X |
| Demographics | X |  |  |  |  |  |  |  |  |
| Social Demographics | X |  |  |  |  |  |  |  |  |
| Previous drug therapy- ADHD | X |  |  |  |  |  |  |  |  |
| Previous drug therapy- all other  CNS Therapies | X |  |  |  |  |  |  |  |  |
| Concomitant medications | X | X | X | X | X | X | X | X | X |
| Adverse events | X | X | X | X | X | X | X | X | X |
| Dispense drug |  | X | X | X | X | X | X | X |  |
| Study drug compliance |  |  | X | X | X | X | X | X | X |
| **Investigator-Administered Scales:** | | | | | | | | | |
| ASRS (prior to v1 via web) | X |  |  |  |  |  |  |  |  |
| SCID-RV | X |  |  |  |  |  |  |  |  |
| ACDS v1.2 | X |  |  |  |  |  |  |  |  |
| CAARS-Inv-SV | X | X | X | X | X | X | X | X | X |
| CGI-ADHD-S | X | X | X | X | X | X | X | X | X |
| MADRS | X |  |  | X |  | X |  |  | X |
| **Patient-Rated Scales: d** | | | | | | | | | |
| AAQOL-29 |  | X | X | X | X | X |  |  | X |
| CAARS-S:SV | X | X | X | X | X | X | X | X | X |
| PGI-I |  |  | X | X | X | X |  |  | X |
| Habits Timeline Followback: (Alcohol, Nicotine, Caffeine, Marijuana, and Drug) |  | X | X | X | X | X |  |  | X |
| Fagerstrom Test for Nicotine  Dependence |  | X |  | X |  | X |  |  | X |
| SASS |  | X |  | X |  | X |  |  |  |
| Driving Behavior Survey - Self  Report |  | X |  | X |  | X |  |  |  |

|  |  | |  | | | |  | | |
| --- | --- | --- | --- | --- | --- | --- | --- | --- | --- |
| **Study Period** | **I** | | **II** | | | | **III** | | |
| **Visit** | **1** | **2** | **3** | **4** | **5** | **6**  **SUM IIa** | **7** | **8** | **9**  **SUM IIIa** |
| Driving Behavior Survey - Other  Report |  | X |  | X |  | X |  |  |  |
| BRIEF-A |  | X |  | X |  | X |  |  |  |
| Epworth Sleepiness Scale |  | X | X | X | X | X |  |  | X |
| Beck Anxiety Inventory |  | X |  | X |  | X |  |  | X |
| **Laboratory Measures:** | | | | | | | | | |
| Chemistry e | X |  |  |  |  | X |  |  | X |
| Hematology e | X |  |  |  |  | X |  |  | X |
| Cotinine e | X |  |  |  |  | X |  |  | X |
| TSH e | X |  |  |  |  |  |  |  |  |
| Urinalysis e | X |  |  |  |  | X |  |  | X |
| ECG | X |  |  |  |  | X |  |  | X |
| CYP2D6 f |  |  |  |  |  |  |  |  |  |
| Blood Alcohol Screen e | X |  |  |  |  |  |  |  |  |
| Urine Drug Screen e, g | X |  |  |  |  |  |  |  |  |
| Pregnancy test e, h | X |  |  |  |  |  |  |  |  |

Abbreviations: X = required at this visit; AAQOL-29 = Adult ADHD Quality of Life Scale 29-item; ACDS = Adult ADHD Clinician Diagnostic Scale version 1.2; ASRS = Adult ADHD Symptom Rating Scale; BRIEF-A = Behavior Rating Inventory of Executive Function-Adult Version-Self; CAARS- Inv:SV = Conners’ Adult ADHD Rating Scale-Investigator Rated: Screening Version; CAARS-S:SV = Conners’ Adult ADHD Rating Scale-Self-Report: Screening Version; CGI-ADHD-S = Clinical Global Impressions –ADHD and Severity; MADRS = Montgomery-Asberg Depression Rating Scale; PGI-I = Patient Global Impression – Improvement; PHQ-9 = Patient Health Questionnaire; SASS = Social Adaptation Self-Evaluation Scale ; SCID-RV = Structured Clinical Interview for DSM-IV Axis Disorders-Research Version.

a Study Period II and Study Period III will have summarization packets for the completion or early

discontinuation from each Study Period.

b A waiver with privacy statement and informed consent (ICD) is obtained prior to patient completing the ASRS and inclusion/exclusion questions via website. An additional online ICD is obtained by the investigator site prior to or at Visit 1 if patient is eligible to proceed to the randomized clinical trial. **Consent must be obtained prior to beginning any medication washout required for the sole purpose of entering this study- even if the washout is commenced prior to Visit 1.**

c Presenting/preexisting conditions does not include symptoms of ADHD.

d The Patient-rated outcome measures scales (e-PROS) may be completed via the internet outside of the doctor’s office. Patients may log into the study website 3 days prior to their originally scheduled visit to start the session to complete planned e-PROS. All patient-rated scales must be completed by the end of the scheduled clinic visit.

e If unsuccessful venipunctures occur or if urine samples cannot be obtained, blood and urine samples

may be collected at an additional visit within 10 days without being considered a protocol violation. However, results from clinical lab tests collected at Visit 1 or this additional visit must be received and reviewed prior to dispensing atomoxetine at the end of Visit 2. Repeat or follow-up laboratory tests may be performed at any time at the discretion of the investigator.

f A blood sample may be drawn assayed for CYP2D6 genotype per investigator request in the event of a clinically significant overdose, serious adverse event (SAE), or if a patient is found to have a new onset of neurological signs and symptom. The Lilly Study Physician must be contacted for approval to draw and analyze the sample

g Urine drug screening and blood alcohol screen are required at Visit 1 and may be performed at any other

visit at the investigator’s discretion.

h For females of child-bearing potential, a serum pregnancy test is required at Visit 1 and may be performed at any other visit at the investigator’s discretion.

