evaluation, a psychiatric evaluation, and a physical examination with a patient history being recorded. Protocol Attachment LYDZ(b).1 contains a complete list of assessment procedures. Clinical assessments conducted during the screening period will include clinical history, Structured Clinical Interview for DSM-IV Axis Disorders-Research Version (SCID-RV; First et al, 2000), and the Adult ADHD Clinician Diagnostic Scale version 1.2 (ACDS v1.2). The CAARS-Inv:SV will also be administered and if the patient’s CAARS-Inv-SV total ADHD symptom score decreases more than 25% between Visit 1  **and** Visit 2, the patient will be discontinued. **Note:** The MADRS will also be administered and a *baseline* score of 3 or greater on Item 10 (Suicidal Thought) of the MADRS is an automatic exclusion from the trial. Exclusion item number [20] outlines details regarding Item 10 of the MADRS administered post-baseline.

If necessary for scheduling or other reasons, the tasks for Visit 1 can be accomplished on

2 separate clinic days. In this case, the date of the visit will be the first of the 2 clinic days and the 2 clinic days must not be separated by more than 14 days. However, if washout of an excluded medication is required, the clinic days can be separated by the time required for appropriate washout of the medication. If the time between Visit 1 and Visit 2 exceeds the visit window interval to allow for washout of medications, this will not be considered a protocol violation.

**Washout.** For patients who have been taking medications excluded by this protocol, the following guidelines for medication washout will apply.

(Special note: informed consent must be obtained prior to beginning any medication washout-even if the washout is commenced prior to Visit 1).

• If the patient is on medication requiring washout on the first day of Visit 1, the ECG and laboratory examinations should be obtained on the second clinic day of Visit 1. The patient must be medication-free for at least 5 half-lives of the drug. The first clinic day will be considered the Visit 1 date.

• Patients who enter the study at Visit 1 taking stimulant medications for the treatment of ADHD must be medication-free for at least 24 hours immediately prior to Visit 2 before diagnostic baseline data/measures are obtained. These medications will also need to be discontinued for the duration of the trial.

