the investigator nor the patient will know when randomization occurs. Further, because of the potential for a double-blind placebo lead-in, any patient randomly assigned to atomoxetine may receive placebo some time during the potential lead-in phase. Patients in the atomoxetine group may receive atomoxetine as early as Visit 2 or as late as Visit 4. The study drug is to be taken by the patient twice-daily, once in the morning and once in the afternoon or early evening. It is strongly recommended to take the study medication with food. Patients randomized to atomoxetine will begin treatment with 40 mg/day (dosed 20 mg twice daily [BID]) for a minimum of 7 days. Immediately following the last dose of 40 mg/day (dosed 20 mg BID), the patient will receive 80 mg/day (dosed 40 mg BID) atomoxetine for a minimum of 7 days. Following Visit 3, one unscheduled

dose decrease is allowed if needed for tolerability or safety. Only one dose decrease will

be permitted during Study Period II.

Starting at Visit 5, if in the judgment of the investigator, the patient has significant residual symptoms, the dose can be increased to the maximum dose of 100 mg/day (dosed 50 mg BID). However, patients who previously required a dose decrease due to safety or tolerability will not be permitted to have a dose increase.

The unscheduled dose decrease or dose increase will only be allowed by one dose level (that is, 80 mg/day to 40 mg/day, 100 mg/day to 80 mg/day, or 80 mg/day to 100 mg/day). Patients unable to tolerate 40 mg/day (dosed 20 mg BID) should be discontinued. Efficacy data and health outcome measures as outlined in the schedule of events will be evaluated.

If the patient has access to the internet, the patient-rated scales (electronic patient- reported outcomes [e-PROS]) may be completed by the patient outside of the investigator’s office. The patient will be permitted to log into the study website 3 days prior to the originally scheduled visit to begin completing patient-rated questionnaires. The patient may log in and out of the study website without losing any data captured at

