the previous login session. If the patient has not completed all of the patient-rated scales on the day of the originally scheduled clinic visit, the patient must complete them at the investigator’s site by the end of the clinic visit. If the patient reschedules the clinic visit, the rescheduled date must occur within the visit interval described in Protocol Attachment LYDZ(b).1. The patient will still be permitted to complete the e-PROs prior to the rescheduled clinic visit IF the visit is within the visit interval window.

**Study Period III:** A 12-week open-label extension period. Patients completing Study Period II will be eligible to enter Study Period III. Patients will be administered open- label atomoxetine at doses of 36 to 100 mg/day that can be taken as QD or BID dosing starting the day after Visit 6.

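### The Visit 2 patient-rated scales, including the only screening-period AAQOL-29, may be completed before the stimulant-free interval that is meant to precede baseline measures.

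*Protocol*

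**What the plan says.** **Early completion.** Footnote d of the Study Schedule (Protocol Attachment LYDZ(b).1) is attached to the heading for all patient-rated scales: "Patients may log into the study website 3 days prior to their originally scheduled visit to start the session to complete planned e-PROS". It sets only a latest time: "All patient-rated scales must be completed by the end of the scheduled clinic visit". Section 7.1, Study Period II, repeats the rule: "The patient will be permitted to log into the study website 3 days prior to the originally scheduled visit to begin completing patient-rated questionnaires". If the appointment moves, "The patient will still be permitted to complete the e-PROs prior to the rescheduled clinic visit IF the visit is within the visit interval window".

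**Washout.** Under Washout in section 7.1, patients who enter at Visit 1 on stimulants "must be medication-free for at least 24 hours immediately prior to Visit 2 before diagnostic baseline data/measures are obtained". Another bullet there, about the ECG and laboratory tests on the second Visit 1 clinic day, says "The patient must be medication-free for at least 5 half-lives of the drug". Exclusion criterion 22 (section 8.2) bars regular psychotropic medication, and the Concomitant Medication List (Attachment LYDZ(b).3) disallows psychostimulants in Study Periods I to III.

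**Baseline.** The Study Schedule collects AAQOL-29 at Visits 2 to 6 and 9, not at Visit 1. Sections 12.2.6 and 12.2.8.1 take baseline from the last of Visits 1 and 2, and section 12.2.8 uses the terms of the primary model for AAQOL-29. Section 12.2.1 defines baseline differently, as the last value before active drug, including the placebo lead-in.

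**The concern.** The washout text shows an intention that baseline be measured off stimulant. The access rule for the questionnaires does not refer to the washout. A patient can therefore open the Visit 2 session, and finish it, before the stimulant-free interval has to start.

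This matters most for AAQOL-29. Its total score is the first gated secondary outcome, its four subscales complete the gated family, and no other screening-period value exists to fall back on. The Visit 2 CAARS-S:SV, SASS, BRIEF-A, BAI, ESS and driving self-report have the same gap. The primary scale, CAARS-Inv:SV, is rated at the site and lies outside the website window.

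At stake are the quality of a baseline covariate and the reading of change from baseline. If stimulant treatment improves reported functioning, an early entry overstates baseline and understates later improvement, equally in expectation in both arms. It also loosens the planned correlation between AAQOL-29 and CAARS-Inv:SV improvement and colours results in patients who entered on stimulants.

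**Working it through.** **1. Timing.** Session opens 3 days before the scheduled visit (footnote d) = 72 h. Minimum stimulant-free interval before Visit 2 (section 7.1) = 24 h. Overlap = 72 − 24 = 48 h. It is longer if Visit 2 is postponed within its window after the session has opened, because login is counted from the original date. If the session opened only after the requirement was met, the overlap would be 0 h.

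**2. The plan's own AAQOL-29 power (section 12.1).** Inputs: 220 per arm, 68% completion, two-sided 5%. Completers per arm n = 220 × 0.68 = 149.6. Power = Φ(ES × √(n/2) − 1.96), with √(149.6/2) = 8.649.

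| Effect size | ES × 8.649 | Power | Stated |
|---|---|---|---|
| 0.325 | 2.811 | 80.3% | 80% |
| 0.35 | 3.027 | 85.7% | 85% |
| 0.40 | 3.459 | 93.3% | 93% |

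The stated figures reproduce on completers. None of the inputs depends on when baseline is recorded.

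**3. Shift in mean baseline.** The documents give none of these inputs, so all are assumptions: 10–30% of patients enter on stimulants, half of them complete early, and full on/off stimulant benefit on AAQOL-29 is 0.3–0.6 SD.

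- If the scale reflected only the moment of completion: 0.10 × 0.5 × 0.3 = 0.015 SD to 0.30 × 0.5 × 0.6 = 0.09 SD overall. Among those entering on stimulants: 0.5 × 0.3 = 0.15 to 0.5 × 0.6 = 0.30 SD.
- If AAQOL-29 looks back one week (assumed; no recall period is stated), completion at Visit 2 after a 24-hour stop still covers about 6 of 7 on-drug days, against 7 of 7 for an early entry. The avoidable part is 1/7: 0.3/7 = 0.04 to 0.6/7 = 0.09 SD per affected patient, and 0.015/7 = 0.002 to 0.09/7 = 0.013 SD overall.

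**4. Loss of precision.** Let a fraction f of patients have baseline shifted by d SD, and let ρ be the baseline–outcome correlation. Baseline variance becomes v = 1 + f(1 − f)d², and the residual SD is multiplied by k = √[(1 − ρ²/v)/(1 − ρ²)].

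At the upper end of step 3 without recall damping, f = 0.30 × 0.5 = 0.15 and d = 0.6, so v = 1 + 0.15 × 0.85 × 0.36 = 1.0459.

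- ρ = 0.5: k = √(0.7610/0.75) = 1.007; power at 0.35 = Φ(3.027/1.007 − 1.96) = 85.2%.
- ρ = 0.7: k = √(0.5315/0.51) = 1.021; power at 0.35 = Φ(3.027/1.021 − 1.96) = 84.3%.

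A deliberately wide grid (f = 0.1–0.5, d = 0.5–1.0, ρ = 0.3–0.7) gives k from 1.001 to 1.092 and power from 85.6% down to 79.2%. Its far corner needs half the trial affected by a full 1.0 SD.

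**5. Bias.** Visit 2 entries precede randomisation, so the share of early, on-drug entries is the same in both arms in expectation. The contrast is not shifted.

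**The case against.** Several counter-arguments have force.

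- **The washout clause already forbids it.** It requires patients to be off stimulant before baseline measures are obtained, and criterion 22 and the medication list point to an earlier stop. So one should not infer that a patient taking a stimulant until 25 hours before Visit 2 is cleanly compliant. This is correct, but it makes the passages contradictory and does not close the gap: footnote d still opens the session, and nothing links access to the washout.
- **The login sentence in section 7.1 stands under Study Period II, while Visit 2 belongs to Period I.** Footnote d is not so limited.
- **Recall periods blunt the effect.** CAARS-Inv:SV, CAARS-S:SV and BAI cover the past week. A reader might infer that clinic ratings at Visit 2 are off-drug and the questionnaires on-drug. That is not supported: after a 24-hour stop the clinic rating also covers mostly on-drug days. The Habits Timeline Followback is a long calendar recall, so a shift of a few days matters little there. This stands and is the main reason to expect a small effect.
- **Section 12.2.1 can give lead-in patients a later baseline.** True under that definition, but the sections specifying these analyses use Visits 1 and 2.
- **The prior-stimulant-use subgroup.** Section 12.2.10 does not equate prior use with use at entry. The 0.15–0.30 SD above applies to the latter and would be diluted in a wider stratum.

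**Conclusion.** The inconsistency is in the text and should be corrected, as a minor point. The Visit 2 session can open up to 48 hours before the stimulant-free interval must begin, and it supplies the only screening-period AAQOL-29 value.

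A reader might go further and set a 0.3–0.6 SD shift in an affected patient beside the 0.325–0.35 effect sizes used for AAQOL-29, concluding that the gated test is compromised. That does not follow. The first is an assumed shift in one patient's change score, common to both arms; the second is a difference between arms. The contrast remains unbiased and the primary endpoint is untouched.

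What is left is a slightly noisier covariate and some distortion of within-arm change, of the improvement correlation and of results in patients entering on stimulants. The size rests on three quantities that the documents do not give (share on stimulants, share completing early, stimulant effect on AAQOL-29) and on an unstated AAQOL-29 recall period. On the assumptions shown, the overall mean baseline moves by 0.002 to 0.09 SD, depending mainly on recall, and power at 0.35 falls by at most about 1.4 percentage points (85.7 − 84.3). Only the far end of the wide grid takes it just below 80%.

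**What to change.** In footnote d and section 7.1, state that for patients washing out an excluded medication the Visit 2 patient-rated session opens only once the protocol's own washout requirement is confirmed, in practice at the clinic on the day of Visit 2. Record the completion time of each session. Keep the 3-day window for later visits. The wording should cover every excluded medication, because section 7.1 ties the SSRI, long half-life and supplement washouts to Visit 2 as well.

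Separately, reconcile the stimulant bullet and the half-lives bullet in section 7.1, exclusion criterion 22 and the Concomitant Medication List on when stimulants must stop. The length of that interval is a clinical decision and is not proposed here.

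The cost is a sentence in each place and a website access setting. The affected patients lose home completion for one visit; section 7.1 already provides for completing the scales at the site.
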